## Abstract

**Background:**

Intrapartum-related death is the third leading cause of under-5 mortality. Effective ventilation during neonatal resuscitation has the potential to reduce 40% of these deaths. Face-mask ventilation performed by midwives is globally the most common method of resuscitating neonates. It requires considerable operator skills and continuous training because of its complexity. The i-gel^®^ is a cuffless supraglottic airway which is easy to insert and provides an efficient seal that prevents air leakage; it has the potential to enhance performance in neonatal resuscitation. A pilot study in Uganda demonstrated that midwives could safely resuscitate newborns with the i-gel^®^ after a short training session. The aim of the present trial is to investigate whether the use of a cuffless supraglottic airway device compared with face-mask ventilation during neonatal resuscitation can reduce mortality and morbidity in asphyxiated neonates.

**Methods:**

A randomized phase III open-label superiority controlled clinical trial will be conducted at Mulago Hospital, Kampala, Uganda, in asphyxiated neonates in the delivery units. Prior to the intervention, health staff performing resuscitation will receive training in accordance with the Helping Babies Breathe curriculum with a special module for training on supraglottic airway insertion. A total of 1150 to 1240 babies (depending on cluster size) that need positive pressure ventilation and that have an expected gestational age of more than 34 weeks and an expected birth weight of more than 2000 g will be ventilated by daily unmasked randomization with a supraglottic airway device (i-gel^®^) (intervention group) or with a face mask (control group). The primary outcome will be a composite outcome of 7-day mortality and admission to neonatal intensive care unit (NICU) with neonatal encephalopathy.

**Discussion:**

Although indications for the beneficial effect of a supraglottic airway device in the context of neonatal resuscitation exist, so far no large studies powered to assess mortality and morbidity have been carried out. We hypothesize that effective ventilation will be easier to achieve with a supraglottic airway device than with a face mask, decreasing early neonatal mortality and brain injury from neonatal encephalopathy. The findings of this trial will be important for low and middle-resource settings where the majority of intrapartum-related events occur.

**Trial registration:**

ClinicalTrials.gov. Identifier: NCT03133572. Registered April 28, 2017.

**Electronic supplementary material:**

The online version of this article (10.1186/s13063-019-3455-8) contains supplementary material, which is available to authorized users.

## Background

### Problem statement

Since 2015, after Millennium Development Goal number 4 (MDG-4), of globally reducing by two thirds the under-5 (years of age) mortality, was summarized, it has become evident that neonatal mortality does not decrease at the same pace as post-neonatal mortality [1].

Of the 140 million babies born in the world annually, 7–9 million will need resuscitation at birth. The latest estimates are that 662,000 deaths annually are caused by intrapartum-related events, commonly referred to as birth asphyxia, which is the third leading cause of under-5 mortality globally [2].

Key health indicators from Uganda in 2017 show that child (under-5) mortality decreased from 175 out of 1000 in 1990 to 53 out of 1000 in 2016 [3]. The rate of neonatal mortality, however, is estimated at 27 out of 1000 and remains unchanged despite the national roll-out of programs such as Helping Baby Breathe (HBB) [3, 4], a basic neonatal resuscitation curriculum for resource-limited settings aiming at improving skilled attendance at birth [5]. HBB implementation trials have demonstrated a reduction in fresh stillbirths and first-day neonatal mortality. However, recent studies in India, Kenya, and Nepal assessing long-term outcomes showed no change in overall 28-day neonatal mortality or perinatal mortality [6, 7].

Sustainable Development Goal number 3 (SDG-3) re-emphasizes the need of accelerating the reduction of neonatal mortality; each country should aim for a neonatal mortality below 12 out of 1000 live births by 2030. Achieving this goal will be possible only if we improve existing neonatal resuscitation programs [8]. All birth attendants, including physicians, midwives, and nurses, should have the knowledge and skills required to perform effective neonatal resuscitation [9]. Innovative tools that can strengthen existing strategies will have to be rapidly implemented if we are to reach the 12 out of 1000 target of neonatal death by 2030.

### Rationale

Providing positive pressure ventilation (PPV) is the single most important component of successful neonatal resuscitation [8, 9]. Yet the mortality of newborns needing face mask (FM) ventilation was as high as 10% in Tanzania [10].

Effective ventilation during neonatal resuscitation has the potential to reduce 40% of intrapartum-related deaths [11]. However, the delivery of proper tidal volume is a difficult technique to master. Mask leakage, airway blockage, and poor chest expansion have been reported during FM ventilation [12–14].

Ventilation is routinely initiated with FM followed by endotracheal intubation in case of FM ventilation failure or need for prolonged ventilatory support. Endotracheal intubation is the most difficult skill to master in neonatal resuscitation and performed only by experienced physicians [15]. The use of endotracheal tube (ETT) is not included in resuscitation guidelines aimed at low-resource settings [16].

The American Heart Association and the European Resuscitation Council guidelines have proposed the use of the laryngeal mask airway (LMA) to replace FM if ventilation is ineffective or as an alternative to ETT during resuscitation of the late-preterm and term infants (at least 34 weeks’ gestation or birth weight of more than 2000 g or both) if intubation is unsuccessful [17].

Several publications, including a recent Cochrane review [18, 19], have shown that the LMA allowed effective PPV in most of the treated patients (range of 95–99%) [20–24], reducing the need for intubation [25, 26]. In previous studies, an inflatable size 1 laryngeal mask was used [21, 23–27].

The i-gel^®^ (Intersurgical Ltd., Wokingham, Berkshire, UK) size 1 is a new model of cuffless supraglottic airway device that has recently been made available for newborns (2–5 kg). It is designed to provide an efficient seal to the larynx without the inflatable cuff used in the traditional LMA. Positioning is easy with a low risk of tissue compression or dislodgement [28–30]. All of these characteristics make the i-gel^®^ a potentially useful alternative to FM and ETT, especially in settings where the staff skills in performing PPV are insufficient [25–27]. A prospective observational study of 50 children demonstrated a success ratio of 100% for the insertion of the i-gel^®^. All devices were inserted on the first attempt. The study showed very few complications and concluded that it seems to be a safe and efficient device for pediatric airway management [31].

Task shifting the use of a cuffless supraglottic airway device to non-doctor or inexperienced health staff in resource-limited settings could be one way to improve outcome following newborn resuscitation. A manikin study in Uganda demonstrated that midwives could easily insert a cuffless supraglottic airway after brief on-the-job training: the i-gel^®^ was also more effective than FM in establishing PPV in the manikin. In 2015, a phase II randomized controlled trial (RCT) on the same site demonstrated that midwives could effectively and safely perform resuscitation in neonates with the i-gel^®^ [32, 33].

The effectiveness and safety of a supraglottic airway device compared with FM, as the primary interface for newborn resuscitation, are still identified as important knowledge gaps. The critical outcomes of mortality and indicators of brain damage also need to be assessed [34]. The proposed trial will follow the SPIRIT (Standard Protocol Items: Recommendations for Interventional Trials) guidelines [35] and provide evidence to determine whether use of a supraglottic airway device translates into better clinical outcomes and thus can be considered part of future guidelines for neonatal resuscitation in resource-limited settings (Additional file 1). The aim of the present trial will be to compare the effectiveness of two interfaces (i-gel^®^ versus FM) for administering PPV at birth in terms of 7-day mortality and neonatal encephalopathy.

## Methods/design

### Trial design

A randomized phase III open-label superiority controlled clinical trial will be conducted in neonates needing PPV at birth with two parallel groups (1:1 ratio): resuscitation with a supraglottic airway device (i-gel^®^) compared to FM (standard of care).

### Setting

This trial will be conducted in Uganda at the Delivery Unit and Operating Theatre of the Department of Obstetrics and Gynaecology at Mulago National Referral Hospital, Kampala, which has about 25,000 annual deliveries.

### Inclusion criteria

Inborn infants fulfilling the following inclusion criteria will be eligible to participate in the trial:Inborn baby (i.e., born in the hospital)Estimated gestational age of at least 34 weeksEstimated birth weight of at least 2000 gNeed for PPV at birth (based on HBB algorithm)Parental consent.

### Exclusion criteria

Major malformations (incompatible with sustained life or affecting the airways)Macerated stillbirth.

### Primary outcome measures

A composite outcome of (a) 7-day mortality or (b) admission to neonatal intensive care unit (NICU) with neonatal encephalopathy (maximum Thompson score of 11 or above at day 1–5 during hospitalization) or both [36–38].

### Secondary outcome measures

Safety of i-gel^®^ in the hands of lower cadre (non-doctor) birth attendants: adverse events (AEs) and serious adverse events (SAEs)Time to initiate PPVHeart rate at 0, 60, 90, 120, 180, 240, and 300 sAdvanced resuscitation (chest compressions, intubation, and drug delivery), including intervention by supervising physicianEarly neonatal death (<7 days)Very early neonatal death (<24 h)Neonatal encephalopathy: admission to NICU with a Thompson score of 11 or above during day 1–5 during hospitalizationNeonatal encephalopathy: admission to NICU with a Thompson score of 7 or above at day 1–5 during hospitalizationAny hospital admission during the first 7 days of life.

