### Sample size

Considering our previous phase II trial, we estimate that a reduction of 25% of adverse outcomes may be possible. A sample size of 954 participants (477 per arm) is required to have a 90% chance of detecting, as significant at the 5% level, a decrease in the primary outcome measure from 40% in the standard-of-care arm to 30% in the supraglottic-airway arm. The sample size is increased to 1150 or 1240 because of the day-by-day cluster randomization, assuming an intra-class correlation of 0.10 and an average daily enrollment of three or four participants, respectively.

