### Data collection and monitoring

#### Assessment and collection of outcomes

The primary outcome will be assessed in two parts. Mortality outcome will be collected daily at the NICU for admitted trial patients until day 7. Non-hospitalized participants will receive a scheduled appointment or phone call by a trial nurse with the mother at day 7 assessing the health of the baby. For all hospitalized participants, morbidity by neonatal encephalopathy will be assessed by a trial doctor masked to the arm allocation. This assessment will take place daytime on day 1, 2, 3, 4, and 5 or until discharge, using Thompson score (Table 1).

**Table 1 Tab1:** Timeline of the trial

	Enrollment	Allocation	Admission neonatal intensive care unit		Follow-up
Time point	T-1	Day 0	Day 1	Day 2–5	Day 7
Enrollment					
Eligibility screen	×				
Prior oral consent	×				
Deferred consent			×		
Randomization		×			
Interventions					
Resuscitation		×			
Assessments					
Active monitoring of resuscitation		×			
Video recording		×			
Neurological status			×	×	
Mortality assessment			×	×	×

Data from the pre-coded case report form (CRF) will be entered into Open Data Kit (ODK) (https://opendatakit.org), an open-source suite of tools that helps researchers manage mobile data collection solutions. The data will be stored on an encrypted server and subsequently transferred to a statistical software package for analysis.

The CRFs will be pre-tested before the commencement of the trial. Data from the birth attendants’ questionnaire and the CRFs will be filled in by the birth attendants and will be continuously entered into ODK.

Videos will be recorded as a quality control. The neonatal resuscitation algorithm will be put in place to ensure that all interventions are standardized. A proper light source is needed on the table. Headlamps will act as backup in case of a power shortage at night.

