### Statistical analysis

A detailed statistical analysis plan—based on the principles in this section—will be developed before the statistical analysis of the trial. Data analysis will be performed by using the statistical software packages Stata, SAS, and R. All tests will be two-sided, and a *P* value of less than 0.05 will be considered statistically significant. Missing data will be considered, and appropriate imputations will be discussed and performed when appropriate. Statistical analysis will include an unadjusted analysis followed by an adjusted analysis. The primary outcome will be compared between the two treatment arms by using the chi-squared test. The secondary outcomes will be compared by using the chi-squared test or Fisher’s test (categorical outcomes) and using the Student’s *t* test or Mann–Whitney test (continuous outcomes). Mixed-effect regression models will be estimated to evaluate the effect of the treatment on binary outcomes, adjusting for clusters (random effect) and clinically relevant confounders. Data analyses will be performed on an intention-to-treat (ITT) basis. However, since the trial is prone to some contamination (i.e., the person resuscitating may decide to shift to the other device) which can be limited by appropriate training but not entirely prevented, a per-protocol analysis and a contamination-adjusted ITT analysis will also be performed. These results will be considered along with the primary ITT analysis when drawing the conclusions of the trial. Subgroup analyses—per treatment center, time of the day (i.e., day/night), and per birth mode—will be carried out with exploratory purpose.

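### The stand-alone encephalopathy and admission outcomes cannot register a baby who dies first, so they are biased against a device that prevents early deaths

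*Protocol article*

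**What the plan says.** All references are to the protocol article.

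- **Primary outcome measures.** Death is an event: "A composite outcome of (a) 7-day mortality or (b) admission to neonatal intensive care unit (NICU) with neonatal encephalopathy", the encephalopathy part requiring a maximum Thompson score of at least 11 on days 1 to 5.
- **Secondary outcome measures.** Encephalopathy appears alone at two thresholds: NICU admission with a Thompson score of at least 11, and "admission to NICU with a Thompson score of 7 or above". Any admission in the first 7 days is a further outcome. Death is a component of none of the three. Death before 7 days and death before 24 hours are listed as outcomes of their own.
- **Assessment and collection of outcomes.** Scoring is limited to admitted babies: "For all hospitalized participants, morbidity by neonatal encephalopathy will be assessed by a trial doctor masked to the arm allocation". It takes place in daytime from day 1. Table 1 puts resuscitation on day 0. Mortality is collected to day 7 for admitted and non-admitted babies.
- **Statistical analysis.** Analysis is by intention to treat. Categorical secondaries are compared by chi-squared or Fisher tests, and mixed models are added for binary outcomes. The significance rule covers every test: "All tests will be two-sided, and a *P* value of less than 0.05 will be considered statistically significant".
- **Exclusion criteria.** Only macerated stillbirths and certain major malformations are excluded, so babies who die in the delivery unit can be in the trial.

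**The concern.** Each of the three outcomes requires the baby to live long enough to be admitted, and the two encephalopathy outcomes also require survival to the first score. Over all randomized babies, an early death is therefore a non-event, the same as a healthy baby who was never admitted. If the device turns an early death into a surviving baby with encephalopathy, the outcome count in its arm rises although the baby has gained.

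Restricting the denominator to admitted babies does not cure this. Admission and survival to scoring come after randomization and may depend on the device, so the arms would no longer be comparable. The mixed models inherit the same problem, because it lies in the outcome definition and not in the test.

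This bears on interpretation because the Discussion hypothesizes lower early mortality and less brain damage from encephalopathy. The stand-alone encephalopathy comparisons are the natural place for a reader to look for the second of these. For Thompson 11 the primary composite supplies a version that counts death. For Thompson 7 no listed outcome does.

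**Working it through.** **Step 1. The plan's own figure.** The Sample size section states "A sample size of 954 participants (477 per arm) is required to have a 90% chance of detecting" a change "from 40% in the standard-of-care arm to 30% in the supraglottic-airway arm". With two-sided 5%, pooled variance and no continuity correction:

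n = [1.960·√(2·0.35·0.65) + 1.2816·√(0.40·0.60 + 0.30·0.70)]² / 0.10² = 476.01, rounded up to 477 per arm, or 954 in total.

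The inflation is stated as "assuming an intra-class correlation of 0.10 and an average daily enrollment of three or four participants, respectively". The design effect is 1 + (m − 1)·0.10, so m = 3 gives 1.2 × 954 = 1144.8 (stated 1150) and m = 4 gives 1.3 × 954 = 1240.2 (stated 1240). The calculation reproduces. It concerns the composite only and does not bear on this point.

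**Step 2. Formula.** Let:

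- NE0 = control risk of encephalopathy at the chosen threshold
- d0 = control risk of death before admission or first score
- s = share of those deaths prevented by the device
- q = share of rescued babies who reach the threshold
- R = the device's risk ratio for encephalopathy in all other babies

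Over all randomized babies:

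- stand-alone risk on the device = NE0·R + d0·s·q
- early death or encephalopathy on the device = that risk + d0·(1 − s), against NE0 + d0 on control

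The term d0·s·q is never negative, so the bias always runs against a device that prevents early deaths. The direction reverses only when d0·s·q exceeds NE0·(1 − R).

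**Step 3. Numbers.** The documents give none of these five inputs, so all are assumptions: NE0 = 30%, s = 50%, q = 75%.

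| d0 | Device risk, R = 1 | Ratio, R = 1 | Ratio, R = 0.90 | Ratio, R = 0.75 | Early death or encephalopathy, R = 1 |
|---|---|---|---|---|---|
| 2% | 30.75% | 1.03 | 0.93 | 0.78 | 32.0% to 31.75% |
| 5% | 31.88% | 1.06 | 0.96 | 0.81 | 35.0% to 34.4% |
| 10% | 33.75% | 1.13 | 1.03 | 0.88 | 40.0% to 38.75% |

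Example, d0 = 10% and R = 1: 0.30 + 0.10·0.50·0.75 = 0.3375, and 0.3375/0.30 = 1.125.

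Over a wider range (s 25% to 50%, q 50% to 100%, d0 2% to 10%) the ratio runs from 1.01 to 1.17 with R = 1, and from 0.76 to 0.92 with R = 0.75.

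**Step 4. Break-even.** The relative reduction in other babies that cancels the bias is d0·s·q/NE0: 2.5%, 6.3% and 12.5% for d0 of 2%, 5% and 10%.

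**Step 5. Any admission.** Suppose every rescued baby is admitted, there is no other effect, s = 50% and control admission is A. The ratio is (A + 0.5·d0)/A. For A from 40% to 80% and d0 from 2% to 10% it runs from 1.01 (0.81/0.80) to 1.13 (0.45/0.40).

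**Step 6. Would a test flag it?** Take the largest R = 1 case in the table, 30% against 33.75%, with 620 per arm. The pooled risk is 0.31875 and the standard error √(0.31875·0.68125·2/620) = 0.0265, so z = 1.42 and p is about 0.16. With a design effect of 1.3, p is about 0.21.

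**The case against.** A reader might infer that a device which saves the sickest babies will look harmful. The documents do not support that. The trial is planned on a 25% relative reduction. If a reduction of that size also holds for encephalopathy in the other babies, the stand-alone ratio stays below 1 in every scenario run. A cut of 2.5% to 12.5% already cancels the bias under the assumptions in the table.

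Nor would a significant result in the wrong direction be expected: step 6 gives a p-value well above 0.05 even in an unfavourable case.

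It is also tempting to take the 10% mortality quoted under Rationale as the early-death risk. That figure is for mask-ventilated newborns in another country and has no timing relative to admission. Only deaths before admission or first score matter, and babies who die after being scored can still count. A one-for-one shift is the upper limit, since it needs every rescued baby to reach the threshold.

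The article also states no denominator or rule for death in these outcomes, and an analysis plan could add one. That stands, but neither available denominator repairs a definition in which a dead baby cannot be an event.

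Two further points stand. Death is reported beside these outcomes, so a careful reader can see the competing event. And admission can be read as a measure of care use, for which merging in death would change the question.

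**Conclusion.** The point holds as a bias of known direction and modest, uncertain size. Early death precludes all three outcomes, so a device that prevents early deaths is judged too unfavourably on them. The estimate may be diluted (0.78 to 0.88 where the effect in other babies is 0.75), close to neutral (0.93 to 1.03 where it is 0.90), or above 1 (1.03 to 1.13) if nothing is prevented in other babies. These figures rest on assumed inputs and on a model that leaves out deaths after scoring. The primary composite is not affected, and neither are the separate mortality outcomes. This is a minor but inexpensive improvement, most useful for Thompson 7, where no listed outcome includes death.

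**What to change.** - In place of the stand-alone Thompson 7 outcome, test a composite in all randomized infants: death within 7 days, or NICU admission with a Thompson score of 7 or above on days 1 to 5.
- Report stand-alone Thompson 11 or above, stand-alone Thompson 7 or above and any admission descriptively. For each, tabulate death, event and neither by arm over all randomized infants, and do not read them as separate efficacy tests.
- Keep admission as its own descriptive outcome. Merging death into it is a trade-off, because it would no longer describe use of care.

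No new data are needed, since mortality to day 7 is already collected for admitted and non-admitted babies. The costs are more overlap between the new Thompson 7 composite and the primary outcome, and a documented change to a secondary outcome definition in a trial that began recruiting in May 2018. The change should be dated and made before allocation is unmasked for analysis.

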### Procedures

#### Prior to interventions: training midwives

Two hundred members of the staff involved in neonatal resuscitation participated in a modified HBB (2nd edition) one-day course [5] during two weeks in November 2017. The course was held by two pediatricians familiar with the use of supraglottic airway devices and was facilitated by two or three local HBB instructors. It consisted of a review of the HBB action plan and practical hands-on skill stations. The HBB training includes simulation scenarios involving key procedures of the action plan (thermal loss prevention, stimulation, clinical assessment, airway management, etc.) and the use of the FM (Laerdal silicon resuscitator, Laerdal Medical, Stavanger, Norway). An additional module for training on the use of the i-gel^®^ (Intersurgical Ltd.) was added. A high-fidelity model (SimNewB Laerdal manikin, Laerdal Medical) was used to train the staff in the use of both devices (i-gel^®^ and FM). SimNewB provides realistic airways and good feedback with chest rise when effective PPV is provided. The participants learned the insertion technique recommended by the manufacturer that is the same in the manikin and in the neonate [26, 32]. A silicon lubricant (not needed in newborn infants because of oral secretions) facilitated the procedure. Three successful i-gel^®^ insertions in the manikin were required to partake in the study. FM ventilation was taught in accordance with the HBB curriculum using the NeoNatalie manikin (Laerdal Medical) and included advanced corrective measures. In case of failed FM ventilation, the participants were instructed to apply the following measures before considering the alternative airway device: reapplication of the mask, repositioning of the head, and increase of the inspiratory pressure. The use of suctioning was de-emphasized in accordance with the latest guidelines.

